### Sample Size

There are currently no comparative studies investigating the influence of humanoid robots on the motivation of people with dementia. Therefore, no results can be used to calculate an optimal sample size. However, to gain insight about what is feasible with our sample size, we estimated the possible effect size. For simplicity, sample size considerations are based on a Student’s *t* test. A sample size of 20 in each group will have 80% power to detect an effect size of 0.91 using a two-group *t* test, with a 5% two-sided significance level. For example, if there is a mean difference of 10 between the groups and a standard deviation of 11 (the latter being assumable according to the literature [32]), the effect size would be 0.91. As a drop-out rate of 20% to 30% can be assumed, 20 people with dementia per group was planned (40 in total). This is the maximum number of people that can be realized with two robots during the study period of 10 months. Beside the people with dementia, their main relatives will be included (n=40, 20 each group) and as a supplement five nurses, nursing assistants, and dementia trainers, respectively, will be included. A small sample size of nursing staff and dementia trainers were chosen because a minimum of three people are necessary for usability tests (which is one focus in the study), if there are more than three groups included [33]. The inclusion of these further two groups was necessary to get an in-depth understanding of using robots in home care.

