### Randomization and Blinding

A randomization plan will be prepared by the Institute of Medical Informatics, Statistics and Documentation at the Medical University of Graz. For that, randomization software will be used. Only authorized people will be able to randomize patients, and the allocation to the intervention and control group will be balanced. There are two robots available for simultaneous use in the study, therefore, four people will always be randomized (two for intervention and two for the control group) two weeks before the next round starts. This will be done until all 40 people have been randomized. A single blinding will be performed. The clinical health care psychologist who will perform data collection before and after the interventions will be blinded.

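### The 80% power at an effect size of 0.91 holds for 20 evaluable people per group, but only 20 per group are randomised and 20-30% drop-out is assumed

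*Protocol article*

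**What the plan says.** All the figures are in one paragraph of the protocol article, Sample Size. It explains that no comparable studies exist from which to derive a sample size, and that an effect size was therefore estimated for the sample available. The method is a deliberate simplification: "For simplicity, sample size considerations are based on a Student’s" t test, "with a 5% two-sided significance level". The result is: "A sample size of 20 in each group will have 80% power to detect an effect size of 0.91". An example follows: "if there is a mean difference of 10 between the groups and a standard deviation of 11", which gives the 0.91.

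The next sentence turns to attrition: "As a drop-out rate of 20% to 30% can be assumed, 20 people with dementia per group was planned (40 in total". The paragraph then says that 40 is as many people as two robots can serve in the 10-month study period.

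Randomization and Blinding confirms that 40 is the number randomised, not the number completing: "This will be done until all 40 people have been randomized". Each round takes four people, "two for intervention and two for the control group", so allocation is 1:1. The article describes no replacement of drop-outs. The Measurements section assures only sample characteristics, such as age, gender and education, from a person who leaves after randomisation.

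**The concern.** The drop-out sentence reads as though 20 per group had been chosen to absorb a 20-30% loss. But 20 is also the number in the power statement, which makes no deduction. Both statements can hold only if the loss costs no outcome data.

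At stake is how the trial's sensitivity is understood. A reader of a null result would take 0.91 as the effect the trial had an 80% chance of detecting. Under the paragraph's own drop-out assumption, the chance of missing that effect is nearer 30-36% than 20%.

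**Working it through.** **Inputs** (Sample Size, and Randomization and Blinding): two-sided alpha 0.05; unadjusted two-group t test; 1:1 allocation; difference 10, SD 11; 20 randomised per group; drop-out 20-30%.

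**Formulas.** Effect size d = difference / SD. With n evaluable per group, the test statistic has 2n - 2 degrees of freedom and noncentrality d × √(n/2). Power is the probability that a noncentral t with these parameters exceeds the two-sided 5% critical value in absolute size. The detectable effect is the d for which this probability is 0.80.

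**Step 1: reproduce the plan's figure.** d = 10/11 = 0.909, rounded to 0.91. With n = 20, there are 38 degrees of freedom and the noncentrality is 0.91 × √10 = 2.88. Power is 80.1% (80.0% at d = 10/11). The stated 80% is reproduced. Solving for n at 80% power gives 19.96, so 20 evaluable per group is the minimum and any loss takes power below 80%.

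**Step 2: apply the stated drop-out.** 20 × (1 - 0.20) = 16; 20 × (1 - 0.30) = 14.

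| Evaluable per group | Noncentrality at 0.91 | Power at 0.91 | Effect detectable with 80% power | Difference at SD 11 |
|---|---|---|---|---|
| 20 (no loss) | 0.91 × √10 = 2.88 | 80.1% | 0.91 | 10.0 |
| 16 (20% loss) | 0.91 × √8 = 2.57 | 70.2% | 1.02 | 11.3 |
| 14 (30% loss) | 0.91 × √7 = 2.41 | 64.0% | 1.10 | 12.1 |

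The type II error at 0.91 is 100 - 70.2 = 29.8% to 100 - 64.0 = 36.0%, against a nominal 20%.

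**Step 3: what an allowance would have required.** 20 / 0.80 = 25 and 20 / 0.70 = 28.6, so 25-29 randomised per group, or 50-58 in total. With two robots and a four-week cycle (three weeks of use, one week of changeover), 20 intervention households take 10 rounds, or 40 weeks. Twenty-five would take 13 rounds (52 weeks) and 29 would take 15 rounds (60 weeks). Neither fits a 10-month study.

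**Step 4: sensitivity to equal loss.** With 28 evaluable in total, a 16/12 split gives 63.1% and a 17/11 split 62.0%, against 64.0% for 14/14. With 32 in total, 18/14 gives 69.5% and 20/12 gives 67.4%, against 70.2% for 16/16. Imbalance lowers power slightly.

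**The case against.** The strongest reply is that no stated number is wrong. The 80% reproduces, and the paragraph never says that it survives drop-out. It offers the calculation as an indication of what the available sample could show, and names robot capacity as the limit. All of that stands. The fault is narrower: two adjacent statements use the same 20 for different purposes, and the drop-out sentence presents as an allowance something that is not one.

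Second, drop-outs might still supply outcomes. Measurements sets a minimum of data, not a maximum, and Quantitative Analysis follows intention to treat. This stands in part, so 64-70% is conditional. But outcome data from drop-outs are not assured, Table 1 ticks questionnaires only before and after the three weeks, and intention to treat does not supply a missing post-intervention score.

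Third, the primary analysis is a median regression that can be adjusted for degree of dementia and depression, not a t test. This stands, and it cuts both ways. Ignoring the degrees of freedom spent on covariates, a correlation between covariates and outcome of √(1 - (0.91/1.024)²) = 0.46 with 16 per group, or √(1 - (0.91/1.100)²) = 0.56 with 14, would bring a mean-based analysis back to 80%. Conversely, comparing medians is less efficient than comparing means if the data are normal. The article gives no figures to settle the balance.

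A reader might also infer that the detectable effect is the only justification for the trial's size. The paragraph does not support that, since capacity sets the size.

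**Conclusion.** The point holds as a failure to carry the assumed drop-out into the power statement. The 80% at 0.91 applies to 20 evaluable per group, exactly the number randomised, with no slack. Under the assumed 20-30% loss, power at 0.91 is about 64-70% and the effect detectable with 80% power is about 1.02-1.10. These figures rest on three assumptions: drop-outs yield no post-intervention outcome, loss is equal between groups, and the test is the protocol's unadjusted t test.

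Two stronger readings are not supported. A reader might treat 64-70% as the trial's actual power; the planned analysis differs from the t test, so the range shows only the effect of loss on the protocol's own approximation. A reader might also express the differences in points on the Apathy Evaluation Scale. That is plausible because the scale measures motivation, but the sample size paragraph names no scale for the 10 and the 11, so they are left unlabelled here.

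Severity is moderate. Capacity sets the size, the figure is a feasibility estimate, and the trial could detect only a large effect either way.

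**What to change.** Leave enrolment unchanged and replace the power and drop-out sentences in Sample Size with wording such as:

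> Twenty per group, the maximum possible with two robots, will be randomised. With 20-30% drop-out, 14-16 per group are expected in the analysis. For simplicity based on a two-group t test (the primary analysis is a median regression, so actual power may differ), this gives 80% power for an effect size of about 1.02-1.10 and about 64-70% power for 0.91. The 80% figure for 0.91 holds only if all 20 per group are evaluable.

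If the worked example is kept, add that at SD 11 the detectable difference is 11.3-12.1 after the assumed loss, and name the scale to which it refers.

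The cost is wording only. Recruitment, randomisation, procedures and analysis are unaffected; the stated sensitivity becomes less favourable.

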### Recruitment

The recruitment of the participants will be carried out by project members of a social nonprofit organization in the community. The sampling method will be convenience sampling. This organization runs the first dementia service center in Styria and offers advice and consultation for relatives providing care at home. They also offer Morbus Alzheimer Syndrome training in private households. All potential participants will be contacted personally or by telephone by the nonprofit organization. Interested participants will be offered a home visit to inform them in detail about the study by means of an information folder (including detailed information about the study) and a short video about the robot Pepper. For the recruitment, flyers will be placed at the service points of the social nonprofit organization, at the organization’s regional events, in waiting rooms of medical practices, and on social media platforms. Only participants who were willing to be assigned to either the intervention or control group were included.

### Randomization and Blinding

A randomization plan will be prepared by the Institute of Medical Informatics, Statistics and Documentation at the Medical University of Graz. For that, randomization software will be used. Only authorized people will be able to randomize patients, and the allocation to the intervention and control group will be balanced. There are two robots available for simultaneous use in the study, therefore, four people will always be randomized (two for intervention and two for the control group) two weeks before the next round starts. This will be done until all 40 people have been randomized. A single blinding will be performed. The clinical health care psychologist who will perform data collection before and after the interventions will be blinded.

### Ethics Approval and Consent to Participate

This study follows the Declaration of Helsinki and received ethical approval from the Ethics Committee of the Medical University of Graz, Austria (Approval Number: 30-401ex17/18). For all participants, written informed consent by project members of the social nonprofit organization will be obtained. If people with dementia have a legal representative, the written informed consent will be given by them. If a person with dementia is not able to give written informed consent by themselves and has no legal representative, he or she will be not included in the study. Every person with dementia and all robots will be insured during the study. The participants can drop out of the study at any time, and in the event of health hazards, the study will be stopped immediately for the affected person.

### Interventions

#### Robot Pepper

Pepper is a humanoid SAR from the company SoftBank Robotics. Pepper is 1.20 m tall and weighs 28 kg. Pepper has four microphones, two high definition cameras, and a depth-perceiving sensor that gives Pepper three-dimensional sight of his surroundings. Pepper talks in different languages like English, French, and German, and it has a touchscreen tablet on its torso. An internal gyro sensor gives Pepper information about the position of its body. Pepper can make fluid and expressive movements with its arms, and while the hands are equipped with touch sensors, Pepper is unable to pick up objects. Furthermore, Pepper has 3 bumper sensors and laser sensors as well as sonars to estimate distances to obstacles. Omnidirectional wheels enable Pepper to move and rotate on the spot. Robot Pepper is not able to navigate in rooms because of software restrictions. Peppers’ operation time is about 12 hours. For this study, the functions of Pepper were refined according to the results of a prior qualitative study with the aim of exploring the needs of people with dementia and a follow-up pilot study where the first refined prototype was tested (mainly for acceptance regarding the robot’s usability). The functions of the refined Robot Pepper can be seen in Figure 1.

#### Tablet PC–Based Dementia Training

The training program was developed in a prior study for people with dementia living at home or in institutional care. The training includes a serious game with a cognitive and physical training program, and the training can be tailored to an individual (eg, content, level of difficulty adapted to the stage of dementia, procedure, and time). The training always starts first with physical exercises (eg, balance, motor skills, and coordination), which are explained by text and video on a tablet PC. This is followed by cognitive exercises, including quizzes, spot-the-difference puzzles, puzzles, looking for picture pairs, cloze tests, mathematical tasks, listening tasks, and songs.

#### Intervention Group (Coach Pepper)

For the intervention group, the robot Pepper is virtually connected via Web interfaces with the dementia training program on an additional tablet PC. Therefore, the intervention group is called a Coach Pepper group (Figure 1).

The total study duration is 10 months (three weeks per household). The planned start is May 2019. Because there are two Pepper robots in the study, the robot is transported from the first two private households to the next two private households. This means that the intervention starts with the first two people with dementia, who receive Coach Pepper for three weeks. Thereafter, there is a break of one week when the training and individual adaptation of the robot for the next two households takes place. After this, the next two people with dementia receive the intervention for three weeks. This happens until all 20 people with dementia have received their interventions. Table 1 shows the time schedule of the study.

**Table 1 table1:** Time schedule: an example of two study rounds.

Study phases		Enrollment (Ongoing)	Randomization/allocation (2 weeks before intervention)	(Break)	Study round 1			(Break)	Study round 2			(Break)
				Week 0	Week 1	Week 2	Week 3	Week 0	Week 1	Week 2	Week 3	Week 0
**Enrollment**												
	Eligibility screen	✓^a^	—^b^	—	—	—	—	—	—	—	—	—
	Informed consent	✓	—	—	—	—	—	—	—	—	—	—
	Randomization/allocation	—	✓	—	—	—	✓	—	—	—	✓	—
**Interventions**												
	Coach Pepper	—	—	—	✓	✓	✓	—	✓	✓	✓	—
	Tablet PC–based dementia training	—	—	—	✓	✓	✓	—	✓	✓	✓	—
**Assessments**												
	Questionnaires	✓	—	✓	—	—	—	✓	—	—	—	✓
	Sensor data	—	—	—	✓	✓	✓	—	✓	✓	✓	—
	Observation	—	—	—	✓	—	✓	—	✓	—	✓	—
	Interviews, focus groups	—	—	—	—	—	—	✓	—	—	—	✓

^a^Time of enrollment, intervention, and assessment tasks.

^b^Not applicable.

Due to robot Pepper's restricted mobility (navigation is not possible), the robot will stand on a previously defined place in the household (eg, living room) where the person with dementia spends most of the day. Pepper will start communication proactively when the user is in proximity (person in proximity recognition and proactive dialogs) or by a date and time previously entered (time-triggered proactive dialogs). Pepper will encourage the people with dementia to use the tablet PC–based dementia training, and will guide them through the training with speech, gestures, music, and dance. The physical exercise videos as well as the correct answers for the cognitive exercises will be displayed on robot Pepper’s Tablet. Furthermore, Pepper will motivate the participants to use further functions of Pepper itself. However, it is also possible for people with dementia or their relatives to start Coach Pepper at any time.

During the test phase, a dementia trainer comes to the household once a week for one hour to perform the dementia training together with the people with dementia. A nurse or nursing assistant will also come as a visitor in the first and last week of the test period to perform a one-hour observation of the people with dementia. Outside of these times, the participants can independently use Coach Pepper. In addition, all households will receive regular calls from the research team to discuss questions or issues. For all participants, measurements are taken before, during, and after the intervention period (see Multimedia Appendix 1).

#### Control Group (Tablet PC–Based Training)

The control group will exclusively receive the tablet PC–based dementia training, without the robot. Otherwise, it will be the same procedure as in the intervention group. In total, two people with dementia start the intervention for three weeks, and there will be one week’s break with training for, and adaptations of, the tablet PC–based dementia training for the next two people. Then, a three week test period will happen again with the next two people. This will happen until all 20 people have received the control intervention. Just as in the intervention group, a dementia trainer comes to the household once a week for one hour and a professional caregiver comes twice (first and last week of testing) for observation. Outside these times, people with dementia and their relatives can use the tablet PC training as often as they like. Regular control calls will also be made. For participants in the intervention and control group, it is forbidden during the study to use (similar) devices (eg, robots, tablets, and smartphones) including any cognitive or physical training.

### Training

#### Pepper Master Training

Before the intervention, all responsible project members (eg, dementia trainers, project assistants, and technical people) will receive Pepper Master Training, which will be carried out by the project partner Humanizing Technologies. In this training, Pepper will be presented with its functionalities, including how to unpack, put into operation, and repack the robot. Important notes about the system, daily use, maintenance, and troubleshooting will also also discussed. The training will last two hours. The trained people will be responsible over the course of the project to handle questions/problems from the participants with regard to robot Pepper.

#### Training Data Collection Methods, Course of Study

To ensure consistent data collection, all data-collecting people will be trained by the researchers of the Institute for Nursing Science regarding the course of study, as well as all data collection methods. The duration will be about four hours.

#### Intervention Training

The social nonprofit organization will train their dementia trainers and nursing staff on the interventions with the tablet PC–based training and Coach Pepper. The duration will be about four hours. They will also train the people with dementia and their relatives. The training will be in the private household of the participants on the day of delivery of Coach Pepper or the exclusively tablet PC–based training (first day of intervention, always on Monday). The duration of the training depends on the individual needs of the participants. Every household will receive an operating manual for Coach Pepper and the tablet PC–based training program.

During the study, a hotline will be set up for participants’ questions and problems. Home visits will be offered if problems cannot be solved on the telephone. Furthermore, control calls will be performed regularly by project members to ensure that participants can handle Coach Pepper and the tablet PC–based training program.

### Measurements

An overview of the following data collection methods is outlined in Multimedia Appendix 1. If a participant drops out after randomization, the minimum amount of data collected by this person are the sample characteristics (eg, age, gender, and education). All important changes of measurement methods will be indicated in the trial register. The measurements are shown in Multimedia Appendix 1.

#### Primary Outcome Measurements

##### Motivation

The Apathy Evaluation Scale (AES) will be used to measure motivation because apathy can be understood as a loss of motivation. The scale has 18 items (4-point Likert scale), and a total of 18-72 points can be obtained. Higher scores correspond to a higher degree of apathy, and therefore lower motivation [34,35].

##### Care Burden

The Zarit Burden Interview will be used to measure the subjective care burden of the relatives. The instrument has 22 items (5-point Likert scale), and a total of 0-88 points can be obtained. Higher scores indicate greater caregiver distress [36-38].

#### Secondary Outcome Measurements

##### Quantitative Measurements

###### Quality of Life

The Dementia Quality of Life Questionnaire will be used to measure the health-related quality of life of the people with dementia. The questionnaire consists of a self-rating version for people with dementia with 28 items and a proxy version for their relatives with 31 items. Each version also has an additional item to capture the global quality of life of the person with dementia [39,40]. Both versions are applied during an interview, thus capturing the emotions, memory, and everyday life of the person with dementia during the last week [39,41]. A 4-point Likert scale is used to collect responses and a higher overall total score reflects a better health-related quality of life [38]. For the relatives, the World Health Organization Quality of Life Scale-BREF will be used. It has 26 items and 4 domains (physical health, psychological, social relationship, and environment). For every item, 1-5 points can be obtained. In general, higher domain scores indicate a higher quality of life [42,43].

###### Care Dependency

The Care Dependency Scale will be used to measure care dependency of people with dementia. The scale has 15 items (5-point Likert scale). In total, 15-75 points can be obtained, and lower scores indicate a higher degree of care dependency [44].

###### Mobility

The Timed UP and GO Test (TUG) will be used to measure mobility in people with dementia. The test measures the time (in seconds) an individual needs to stand up from a standard arm chair, walk a distance of 3 m, turn, walk back to the chair, and sit down. Interpretation: <10 seconds=completely unrestricted; 10-19 seconds=less mobile, but still unrestricted; 20-29 seconds=limited mobility; >30 seconds=pronounced mobility restriction; 14 seconds and more has been shown to indicate a high risk of falls [45].

